## 3. Abstract

The Government of Kenya is committed to improving the education of its children, and recognizes the importance of child health for educational achievement. While malaria represents one of the main health problems afflicting Kenyan schoolchildren, the evidence base for policy development and programme implementation for school-based malaria control remains inadequate. A recent study in western Kenya showed that delivering intermittent preventive treatment (IPT) to schoolchildren improved rates of anaemia and classroom concentration, but did not improve school performance. This study aims to (i) investigate the impact of a related malaria prevention strategy, intermittent screening and treatment, on health and education among schoolchildren in a different malaria transmission setting and (ii) determine the interaction between health and improved literacy instruction. The study will be undertaken in 100 randomly selected primary schools in Kwale District. IST will consist of all children being screened using rapid diagnostic tests (RDTs) for malaria once a term (thrice yearly). Children (with or without malaria symptoms) found to be RDT-positive will be treated with artemisinin-based combination therapy (ACT). Screening and treatment will be administered by district health workers. The education intervention will involve a programme of training for primary school teachers to improve literacy instruction. The study is designed to detect a 25% reduction in anaemia and an improvement of 0.2 standard deviations in mathematics and literacy tests. Additional outcomes will also be measured including malaria parasitaemia, classroom attention and school attendance. Health and educational outcomes will be assessed before intervention and twelve and twenty four months later. Information will also be collected on in-vivo parasitological efficacy of treatments and the cost-effectiveness of intervention. The findings of this study will provide critical information on the effectiveness of interventions to reduce the health and education burden of malaria among school-aged children.

#### **4. Background**

Malaria poses an enormous public health burden among the population of Kenya, and several donors are supporting the up-scaling of currently available malaria interventions. Typically, these efforts focus on children under five years and pregnant women because they bear the brunt of morbidity and mortality. However, older children, including those attending school, are also at risk of mortality and morbidity (Lalloo 2006). In addition, malaria greatly contributes to school absenteeism, poor cognition, learning and school performance (Brooker et al., 2000; Holding & Snow, 2001; Lalloo, 2006).

Despite this burden among schoolchildren, there is currently no consensus as to the appropriate approach to malaria control in schools, with relevant intervention strategies likely to vary according to patterns of malaria transmission (Brooker et al., 2008). A promising school-based intervention strategy, already proven effective for improving the health of women in pregnancy, is intermittent preventive treatment (IPT). In a recent study in western Kenya, the mass administration of a full therapeutic course of an anti-malarial drug to schoolchildren once a term, irrespective of infection status, dramatically reduced malaria parasitaemia, almost halved the rates of anaemia, and significantly improved cognitive ability (Clarke et al. 2008; Temperley et al., 2008). The withdrawal in Kenya in 2009 of sulfadoxine-pyrimethamine (SP) and amodiaquine (AQ) from use means that these drugs can no longer be used for IPT. An alternative approach is intermittent screening and treatment (IST), a malaria prevention strategy recently identified in the Kenyan National Malaria Strategy, 2009-2017 as a possible school-based strategy in the newly launched *Malaria Free School Initiative*.

The proposed study will investigate the health and educational impact of school-based IST in a different epidemiological setting in Kenya, where other important contributors to anaemia in school-aged children, including poor nutrition and helminth infections, are important. In addition, the study will investigate a number of scientific and operational issues which yield generate valuable evidence to assist in the formulation of policy recommendations for Kenya and for sub-Saharan Africa.

##### **a) Malaria in schoolchildren**

Although all-cause mortality rates are lowest among school-age children, it is estimated that malaria causes up to 50% of all deaths in this age group in Africa (Snow et al., 2003). Morbidity studies undertaken in western Kenya suggest that between 20% to 50% of schoolchildren living in areas of stable transmission experience clinical malaria attacks each year (Clarke et al., 2004). During malaria epidemics, the incidence of malaria in schoolchildren in areas of unstable transmission may be six times higher than in areas of stable transmission (Clarke et al., 2004). Malaria (both clinical and asymptomatic malaria) is also a major cause of anaemia among school-age children (Kurtzhals et al., 1999), and efforts to control malaria among this age group can dramatically improve haemoglobin levels (Geerligs, Brabin, & Eggelte, 2003).

##### **b) Educational impact of malaria**

In Kenya, primary schoolchildren miss 11% of school days per year because of malaria, and secondary schoolchildren 4% of school days (Leighton & Foster, 1993), equivalent to 4 to 10 million schooldays lost annually (Brooker et al. 2000). Evidence from Sri Lanka found that school performance is related to the cumulative impact of previous malaria attacks (Fernando et al., 2003a) and that weekly chemoprophylaxis with chloroquine improved school examination scores (Fernando et al., 2003b). This impact of malaria was mediated, at least in part, by children's absence from school due to clinical malaria, and it remains unclear from this study whether malaria prevention improved learning processes in the classroom.

In recent study in western Kenya (Clarke et al. 2008) we examined the cognitive processes involved in learning and found that children's sustained attention was improved by IPT. However, this improvement was not translated into improved education achievement over the 12 month course of the study. Possible explanations for this finding are short follow-up (one year) or that children were not given the educational resources (such as textbooks) or a sufficient period of effective instruction to learn effectively during the time course of the study. It is highly plausible that the improved sustained attention we observed in our first study would translate into improved educational achievement, particularly in the early grades of school. Recent evidence (Blair & Razza, 2007) suggests that executive function skills, such as regulation and attention, are particularly important for early achievement. To achieve a measurable impact on education, it may also be necessary to improve teaching methods in order to capitalise on any improvements in health status of schoolchildren following malaria control

In the proposed study we will follow children up for a longer period of time (at least two years) and will also conduct an intervention to improve the quality and quantity of literacy instruction. This will help ensure that children have the opportunity to apply improved cognitive skills and to learn effectively. It will also give us the opportunity to study the interaction between literacy instruction and malaria prevention to investigate whether enhanced instruction is more effective when children are more healthy, and to study the cognitive processes by which this interaction takes place. The role of reading abilities and the teaching methods to develop them is recognized for promoting student success and continual enrollment in school (Jimerson et al., 2000; NICHD, 2000).

### **c) Literacy development**

As in many countries, Kenyan students begin to learn to read in their first year of schooling. Yet, about half of Kenya students who enter primary school drop out before they reach grade 8 (Muthwii, 2004). The drop-out rate could be partially due to low performance in literacy skills (Nzomo et al., 2001).

Kenyan government policy does not mandate that a single teaching method should be used to teach reading (MOEST, 2001). Instead, the policy suggests that the teaching methods should meet the students' learning needs and the objective for the lesson (Commeyras & Inyega, 2007). However, the current approach does not help all enrolled students to learn to read. Nzomo et al. (2001) concluded that about 35 percent of Kenyan students did not reach the designated minimum mastery level of reading and about 77 percent did not reach the desirable level of reading. An intervention to improve the quality of classroom instruction will be designed to ensure that students benefit from literacy instruction that is understood to promote reading acquisition.

Evidence suggests that the critical components of successful literacy acquisition can be taught so that students learn to read more efficiently (Adams, 1990; August & Shanahan, 2006; Snow et al., 1998). When teachers develop their students' oral language skills (e.g., phonological awareness & vocabulary) and teach the relationship between letters and sounds in a systematic and explicit fashion, their students have the foundation for successful word recognition and reading comprehension. Kenyan teachers will be provided with in-service to support their delivery of these foundational literacy skills as well as their assessment these skills in order to optimize student learning.

## **5. Justification for Study**

The Government of Kenya is committed to improving the education of its children, and recognizes the importance of child health for educational achievement. While malaria represents one of the main health problems afflicting Kenyan schoolchildren, the evidence base for policy development and programme implementation for school-based malaria control remains inadequate. A recent proof-of-principle trial in western Kenya has demonstrated the potential of delivering intermittent preventive treatment (IPT) to schoolchildren in order to improve their health and education. In light

of the promising results from this study, it is important to further investigate the benefits of malaria prevention in schools. A change in drug policy in Kenya means that IPT with SP and AQ is no longer a viable strategy, but that there is an important need to evaluate IST, as outlined in the revised National Malaria Strategy, 2009-2017. There is also the need to better understand the educational benefits of malaria prevention before clear policy recommendations can be made. This involves assessing the impact of the alternative strategy of IST on outcomes, such as children's ability to read, which have clear relevance to the aims of education systems. It also involves assessing the extent to which IST increases the effectiveness of improved classroom instruction. The current study will explore whether it is necessary to improve teaching methods in order to capitalise on any improvements in health status of schoolchildren following malaria control. This understanding will yield important information for both health and educational planners as they plan malaria control in school.

## **6. Null hypothesis**

School-based malaria control using intermittent screening and treatment will not reduce rates of anaemia or improve educational outcomes in Kenyan schoolchildren, when compared to a placebo.

In addition, a programme of training for primary school teachers to improve literacy instruction will not improve literacy rates and there will be no interaction between the malaria intervention and the education intervention, such that learning will not be improved when teaching is effective and children are healthy.

## **7. Objectives**

### **a) Overall objective:**

To evaluate the impact of school-based malaria intervention using intermittent screening and treatment (IST) to reduce rates of anaemia among schoolchildren and hence improve classroom attention, school attendance and educational achievement of children in school.

### **b) Specific objectives:**

1. To evaluate the efficacy of intermittent screening and treatment (IST) in improving haemoglobin concentration of schoolchildren.
2. To evaluate the efficacy of IST in reducing rates of asymptomatic malaria parasitaemia of schoolchildren.
3. To evaluate the efficacy of IST in improving classroom attention, school attendance, and educational achievement of children in school.
4. To evaluate the impact of a programme of training for primary school teachers to enhance literacy instruction in improving literacy rates of schoolchildren.
5. To determine whether malaria and education interventions work synergistically together, such that learning is improved only effective teaching is effective and children are healthy to benefit from it.
6. To analyse the cost-effectiveness of IST in improving anaemia and education.

## **8. Design and Methodology**

### **i) General Study design**

This study will be a factorial-design, cluster-randomised, to assess the impact of IST and enhanced literacy instruction by teachers on the health and educational achievement of healthy schoolchildren. This study is one of two studies investigating the health and educational impact of malaria control, with a parallel study planned in Senegal, where malaria transmission is intense but highly seasonal.

The target population in this study includes children attending primary schools in Kenya. The accessible population includes the children attending the participating primary schools in standards 1-7 in Kwale district. The unit of analysis is the school. Schools will be randomized to one of four groups, receiving either the IST intervention alone, the education intervention alone, the IST and education interventions combined, or neither intervention. The first two arms would evaluate the impact of IST. The final two arms would investigate the hypothesis that IST helps children benefit from improved quality of education. Health and educational outcomes will be assessed before intervention and twelve and twenty four months later. The impact of each intervention will be estimated for education outcomes and health outcomes in separate multiple regression models. An interaction term will be included to identify any synergistic effects between the two interventions.

The survey data will be collected over two years – see section 10. Development and testing of survey instruments will take place in 2008. Baseline data collection and intervention activities will commence in January 2009, with follow-up surveys planned in 2010 and 2011. The study will be conducted by the Kenya Medical Research Institute in collaboration with the Division of Malaria Control in the Ministry of Public Health and Sanitation, University of Nairobi, the London School of Hygiene and Tropical Medicine, and Harvard University.

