**v) Sample size determination**

Power analysis was adjusted for clustering (Hayes & Bennett, 1999) and focused on two main outcomes of interest: the percentage of children who are anaemic (haemoglobin <110 g/L); and education achievement assessed by a battery of tests of reading, writing and arithmetic.

For anaemia, assuming a baseline prevalence of 20% (as found in the 2008 school surveys in Kwale), an intraclass correlation of between 0.025 and 50 children sampled per school, a sample size of 21 schools with a total of 1050 children of all ages in each arm was estimated to provide 80% power to detect a 25% reduction in anemia in the intervention group compared to placebo at 5% level of significance. This equates to 84 schools and 4200 children.

For educational achievement tests, an overall sample size of 100 schools with 50 children per school (5000 children overall) is sufficient to detect an effect size of 0.2 standard deviation (SD) assuming an intra-class correlation of 0.2 (ICC varied from 0.1 to 0.2 with mathematics and literacy tests in Class 2 in 210 schools in Western Kenya; ICC is expected to be lower in Class 1) and a correlation between baseline and final test scores of 0.7. This sample size is sufficient to detect an effect size of 0.15 SD for concentration tests, which have a lower intra-class correlation (0.07 in the previous study in Bondo).

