#### 15. Justification of Budget

*Personal salaries and benefits.* This includes salaries and benefits of field coordinators, fieldworkers and technicians.

*Patient costs.* This includes anti-malarials and placebos for all children as well as albendazole, praziquantel, Co-artem and ferrous sulphate, as required.

*Equipment.* This is estimated for the purchase of motorcycles large equipment including microscopes and Hemocue machines.

*Supplies.* This is the estimated cost of all the non-field work supplies required for the study at the KEMRI-Wellcome unit in Nairobi. It includes photocopying, stationary, communication and printing over the survey period. The estimates are based on routine costs charged at the unit.

*Travel and transportation.* During the study preparation an investigator will need to meet with local officials and school head teachers. Travel and accommodation costs for these trips have been factored in here.

The education component of the study involves modifying the way Standard 1 and 2 classroom teachers develop their students' literacy skills. To do this, the intervention includes an initial residential teacher training over a four-day period followed by ongoing monitoring and support. To ensure that all of the school's personnel are informed, the Head Teachers and the Senior Teachers will also be invited to the training. This way, they will be available to support the classroom teachers during the implementation of the intervention. The literacy intervention will be implemented in 50 schools involving at least three teachers from each.

The study has a longitudinal design to investigate the interaction of the malaria intervention and the literacy intervention. To understand the effects of the interventions we will measure students' education achievement at the onset and end of the interventions. Student achievement in 100 schools will be measured. While the surveys are going on, a supervisor, three laboratory technicians, one laboratory technician, one interviewer, one nurse plus one driver will need to travel to the field sites to undertake school surveys. All costs for travel and accommodation have been estimated using standard KEMRI mileage and per diem charges.

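### The arms named for the IST and synergy comparisons contradict the factorial design, no IST contrast is named as primary, and the stated 80% power holds only for pooled arms

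*Protocol*

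**What the plan says.** Section 8 i) calls the trial factorial and lists the arms as "receiving either the IST intervention alone, the education intervention alone, the IST and education interventions combined, or neither intervention". It then assigns arms to questions by position: "The first two arms would evaluate the impact of IST", and "The final two arms would investigate the hypothesis that IST helps children benefit from improved quality of education".

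The same section also plans regression models with an interaction term, and Section 9 (Data analysis) repeats this. Section 8 vii) places the education intervention in half of the IST schools and half of the control schools, which is a true 2×2 layout.

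Section 8 v) gives the anaemia calculation: "a sample size of 21 schools with a total of 1050 children of all ages in each arm was estimated to provide 80% power", for 84 schools and 4,200 children in all. The power is described as "80% power to detect a 25% reduction in anemia in the intervention group compared to placebo at 5% level of significance".

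Placebo also appears in Section 6, where the null hypothesis for IST is framed "when compared to a placebo", and in Section 15 under patient costs: "This includes anti-malarials and placebos for all children".

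**The concern.** In the listed order, the first two arms are IST alone and education alone. They differ in both interventions, so their difference does not isolate IST. The final two are combined and neither. These also differ in both interventions, and their difference mixes both main effects with the interaction.

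The planned regression could resolve this, but the protocol does not say which IST contrast is primary. Section 9 refers to intervention minus control without saying which arms make up each side. With an interaction term and ordinary reference coding, the coefficient labelled IST is the effect in schools without literacy training only, that is, IST alone v neither. That is a third candidate, using half the schools.

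At stake are which effect is reported as the primary result, and whether the stated power applies to it. If the choice is left open until data are seen, the estimate can be selected. The placebo wording is a separate inconsistency: the hypothesis names a comparator that no listed arm receives.

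**Working it through.** **What each contrast estimates.** Write the arm means as: neither = μ; IST alone = μ + a; education alone = μ + b; combined = μ + a + b + c, where c is the interaction.

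| Contrast | Estimates |
|---|---|
| First two arms (IST alone − education alone) | a − b |
| Final two arms (combined − neither) | a + b + c |
| Reference-coded IST coefficient (IST alone − neither) | a |
| Factorial margin (IST alone + combined) v (education alone + neither) | a + c/2 |
| Difference of differences | c |

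As an illustration for educational achievement, if each intervention added 0.2 SD, the first contrast would be 0.2 − 0.2 = 0. For anaemia, teacher training has no evident direct route to the outcome. With b close to 0, a − b is close to a, and the loss there is mainly power.

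**Inputs for anaemia (Section 8 v).** Prevalence 20%; 25% reduction, so 15%; 50 children per school; ICC 0.025 (the only value given); 5% level, taken as two-sided because sidedness is not stated; 80% power. Equal allocation is assumed, so 100 schools give 25 per arm.

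**Reproducing the plan's figure.** The cited cluster-trial formula, with between-school variance expressed through the ICC, is

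schools per side = 1 + (1.96 + 0.84)² × [p₀(1 − p₀) + p₁(1 − p₁)] × (1/50 + 0.025) / (p₀ − p₁)²

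= 1 + 7.849 × (0.16 + 0.1275) × 0.045 / 0.05² = 1 + 40.6 = 41.6, rounded up to 42 per side.

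2 × 42 = 84 schools = 4 × 21. The plan's total is reproduced, with each side made up of two arms.

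**Power by schools per side.** Design effect = 1 + 49 × 0.025 = 2.225. Effective n per side = schools × 50 / 2.225. SE = √(0.2875 / effective n). Power = Φ(0.05/SE − 1.96).

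| Schools per side | Effective n | SE | Power |
|---|---|---|---|
| 21 v 21 (single arms, anaemia plan) | 471.9 | 0.0247 | 53% |
| 25 v 25 (single arms, 100 schools) | 561.8 | 0.0226 | 60% |
| 42 v 42 (pooled, anaemia plan) | 943.8 | 0.0175 | 82% |
| 50 v 50 (pooled, 100 schools) | 1,123.6 | 0.0160 | 88% |

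A t-based check gives 51%, 58%, 81% and 87%. A one-sided test would not rescue the single-arm comparison (65% at 21 v 21, 71% at 25 v 25). At 80% power, the smallest detectable reduction is about 34% for 21 v 21 and 31.5% for 25 v 25, not 25%. A 21 v 21 comparison reaches 80% only if the ICC is about 0.003 or less.

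**Education, for context.** Section 8 v) gives 0.2 SD, ICC 0.2 and a baseline correlation of 0.7, but no power, and does not say at which level the correlation reduces variance. If it acts at both levels, the variance of a school mean is (0.2 + 0.8/50) × (1 − 0.49) = 0.110, and power is 57% at 25 v 25 and 85% at 50 v 50. If it acts only between children within schools, the variance is 0.2 + 0.8 × 0.51/50 = 0.208, and power is 34% and 59%. Under either assumption the single-arm comparison is much weaker.

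**The case against.** The strongest reply is that the two sentences are an arm-ordering slip in a protocol that is otherwise clearly factorial. Section 8 i) itself uses the word, Section 8 vii) crosses the interventions, and Sections 8 i) and 9 assign synergy to an interaction term. Nothing in Section 9 compares IST alone with education alone. A SAP, not shown here, could ordinarily settle the exact contrast.

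Most of that stands. A reader might infer that the trial confounds IST with literacy training; the documents do not support this, because the planned regression can separate the two. A reader might also infer that the trial is too small. That is not supported either: 84 schools is right for pooled arms, and 100 schools exceed it. The 53% and 60% figures apply only if one arm is tested against another.

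Two things remain. The protocol does not leave the contrast to a SAP: it states one, and states it wrongly. And the regression text alone does not recover the margin, since the reference-coded IST coefficient is a 25 v 25 simple effect.

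On placebo, it would be tempting to call the trial open-label or the control unscreened. The protocol never says open-label, and Section 8 xiii) even mentions unblinding. Section 8 viii) provides rapid tests for children with fever without limiting this to IST schools. No IST is as far as the text goes.

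**Conclusion.** The point holds as an internal contradiction with consequences for the primary estimate. The contrasts written in Section 8 i) do not estimate their targets, and they conflict with the factorial analysis described in the same section and in Sections 8 vii) and 9. The confounding is conditional on those sentences governing, and bears mainly on educational achievement, the second primary outcome. The anaemia sample size is correct, but its power statement is true only at the factorial margin; read as a test of one 21-school arm against another, it overstates power by about 27 percentage points (80% against 53%). The stated 80% concerns anaemia only, so the education figures contradict nothing in the plan.

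The placebo references do not cause the confounding or the power gap; they are a separate error in the stated comparator.

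The power figures assume a two-sided 5% test, an ICC of exactly 0.025, equal allocation, no loss to follow-up and no gain from stratification.

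**What to change.** - **Section 8 i):** replace the two sentences. Define the primary IST effect as (IST alone + combined) v (education alone + neither), the literacy effect as (education alone + combined) v (IST alone + neither), and synergy as the difference of differences, tested by the interaction term.
- **Section 8 i) or 9:** state that the marginal IST effect is primary, not the reference-coded coefficient from the model with the interaction.
- **Section 8 v):** state that 80% power for anaemia refers to 42 v 42 pooled schools.
- **Sections 6 and 8 v):** replace placebo with no IST, and reconcile the placebo item in Section 15 with the listed arms.

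The cost is protocol wording only. No schools, visits or procedures are added.
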